Randomization and allocation: Participants are randomized 1:1 (intensified vs. standard dosing) with stratification by admission type (elective vs. emergency), using computer-generated permuted blocks of variable sizes (4, 6, or 8) within each stratum to maintain temporal balance while minimizing allocation predictability. Additional stratification by small bowel resection length was considered but not implemented due to the expected low number of patients with resections ≥50 cm, which would risk creating sparsely populated strata and imbalance in smaller subgroups. Allocation of concealment is ensured via sequentially numbered, opaque, tamper-evident sealed envelopes prepared centrally by a study coordinator who is independent of recruitment, enrolment, and clinical care. Envelopes are identical in appearance, made of non-transparent material, and stored in a secure, access-restricted location within the ward. Each envelope is opened in strict numerical order only after confirming patient eligibility and completing baseline data collection. The envelope method was chosen to enable real-time randomization in a surgical setting while maintaining adequate allocation of concealment. Randomization and allocation are performed by the on-call surgeon or, alternatively, by a study investigator, following training in eligibility assessment, enrollment timing, and the envelope procedure. Due to the nature of the intervention—intravenous omeprazole dosing with specific timing and preparation requirements—and the impracticality of preparing indistinguishable placebo infusions in a busy surgical ward or emergency setting, the blinding of participants and treating clinicians was not feasible. The study is therefore designed as an open-label trial.

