The primary analysis will follow a modified intention-to-treat principle, defined as all randomized participants who underwent ileostomy formation as planned and had stoma output recorded for at least two of the first three postoperative days. The primary endpoint (mean POD 1–3 stoma output) will be calculated using all available daily measurements within this window, with limited missingness handled as specified below.

Continuous variables will be summarized as means with standard deviations or medians with standard deviations or medians with interquartile ranges per distribution; categorical variables as frequencies and percentages. All estimates are presented as two-sided 95% confidence intervals.

The primary efficacy model was prespecified as a parsimonious model including a limited number of covariates in order to preserve statistical power and reduce the risk of overfitting, given the planned sample size. Randomization is expected to achieve a balance of baseline anatomical and clinical characteristics between study groups. Variables potentially influencing absolute stoma output, including resected small-bowel length, study center, use and dose of antimotility agents, and oral or enteral intake volumes, will be prospectively captured in the eCRF. Because the selected post-randomization variables (particularly antimotility use and intake volume) may lie on the causal pathway of the intervention, they will not be routinely included as adjustment covariates in the primary model to avoid the introduction of bias through overadjustment. Instead, these factors will be examined in prespecified exploratory and sensitivity analyses to assess the robustness of findings and potential heterogeneity of treatment effect.

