Secondary outcomes will be analyzed as follows: the incidence of high-output stoma will be compared using the chi-square test; time to output stabilization will be assessed with Kaplan–Meier estimates, the log-rank test, and the Cox proportional hazards model; the incidence of hyponatremia and hypokalemia will be compared using the chi-square test; total potassium supplementation and both index and total length of hospital stay will be compared using two-sided *t*-tests. Prespecified exploratory subgroup analyses will be conducted according to surgical urgency (elective vs. emergency), ileostomy type, and selected baseline characteristics. As the trial is not powered to detect interaction effects, subgroup analyses will be considered hypothesis-generating and interpreted cautiously.

Handling of missing data:

Missing daily stoma output measurements within the POD 1–3 primary endpoint window may occur due to early discharge, ICU transfer, or clinical deterioration.

Cases with two or more missing daily measurements within the primary endpoint window will not be included in the primary analysis and will be reported transparently. In the event of death within POD 1–3, only stoma output data collected up to the time of death will be included.

Missing data will be imputed using multiple imputation by chained equations (MICE), generating 50 datasets under the missing-at-random (MAR) assumption.

The model will include the treatment arm, stratification variable, baseline covariates, observed outputs, co-interventions, and laboratory parameters. Imputation will be performed separately by arm to avoid bias toward the null. Deaths will be recorded and imputed via MICE, with sensitivity analysis excluding deceased patients. For ICU transfers within 48 h or early discharges (before POD 3), MICE will be applied to available data, with subgroup or sensitivity analyses assessing robustness.

Multiplicity control: To control for multiplicity across secondary endpoints, the Bonferroni–Holm method will be applied within two pre-specified endpoint families, Family A: High-output stoma incidence, time to output stabilization, hypokalemia and Family B: Total potassium supplementation, index length of stay, total length of stay.

Definition transparency: The ITT, mITT, and per-protocol populations will be illustrated using decision-tree diagrams in the statistical analysis appendix to ensure reproducibility of analytical decisions.

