## Figures and Tables

**Table 1 jcm-15-01841-t001:** Inclusion and exclusion criteria.

Category	Item	Description
Population		
	Target population	Adults undergoing the formation of a loop or end ileostomy (elective or emergency) at two academic centers in Poland (University Clinical Center, Gdańsk; PCK Maritime Hospital, Gdynia)
Inclusion Criteria		
	Age	≥18 years
	Surgery	Scheduled for formation of a loop or end ileostomy (elective or emergency)
	Consent	Able to provide written informed consent
	Drug suitability	No contraindication to omeprazole or other proton pump inhibitors
Exclusion Criteria		
	Pregnancy/lactation	Pregnancy or lactation
	Drug allergy	Known hypersensitivity or allergy to omeprazole or any other PPI
	Consent impossibility	Inability to provide written informed consent
	Competing trials	Concurrent participation in another interventional study likely to influence outcomes
	Output monitoring	Pre-existing conditions that preclude accurate 24 h stoma output measurement
	ICU/critical illness	Planned or immediate postoperative ICU admission with anticipated ICU stay > 48 h, or any critical illness in which early stomal output is frequently absent
	Investigator judgment	Any situation judged by the investigator to pose unacceptable risk or to confound assessment of the primary endpoint

**Table 2 jcm-15-01841-t002:** Intensified vs. standard omeprazole regimens.

Parameter	Intensified Omeprazole Arm	Standard Omeprazole Arm
Drug	Omeprazole	Omeprazole
Loading dose		
Drug	Omeprazole	Omeprazole
Dose	80 mg	None (standard care)
Route	Intravenous (IV)	N/A
Frequency	Single dose	N/A
Timing	Day before surgery	N/A
Maintenance dose (in-hospital)		
Drug	Omeprazole	Omeprazole
Dose	40 mg	40 mg
Route	Intravenous (IV)	Intravenous (IV)
Frequency	Twice daily (BID)	Once daily (OD)
Administration times	06:00 and 18:00 (±1 h)	06:00 (±1 h)
Duration	Through POD 10 or until discharge	During hospitalization only
Post-discharge continuation		
Drug	Omeprazole	None
Dose	40 mg	Not applicable
Route	Oral (PO)	Not applicable
Frequency	Twice daily (BID)	Not applicable
Duration	To complete 10-day course (if discharged before POD 10)	Omeprazole discontinued at discharge per ward standard protocol
Total treatment duration	10 days (Day of surgery through POD 10)	Variable (Day of surgery through discharge, typically 5–10 days)
Total daily dose		
Day before surgery	80 mg	0 mg
POD 1–10 (or until discharge)	80 mg/day	40 mg/day

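### Randomisation is stratified by admission type, but all three Family B outcomes are tested by t-tests that leave the stratum out, giving up some efficiency if urgency is prognostic

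*Protocol article*

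**What the plan says.** In the protocol article, 3. Analysis, Statistical analyses, the secondary-outcome paragraph fixes the test: "total potassium supplementation and both index and total length of hospital stay will be compared using two-sided" t-tests. The Multiplicity control paragraph applies Bonferroni–Holm within two families, the second being "Family B: Total potassium supplementation, index length of stay, total length of stay". Every member of that family therefore has the same test.

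In 2. Methods, Randomization and allocation, the 1:1 allocation uses permuted blocks within strata, with "stratification by admission type (elective vs. emergency" as the only factor.

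Covariates are mentioned for the primary endpoint only: "The primary efficacy model was prespecified as a parsimonious model including a limited number of covariates". For the secondary outcomes, admission type appears in the imputation model and in exploratory analyses by urgency, but not in the Family B tests. The article lets the data's distribution decide how continuous variables are described (means, or "medians with interquartile ranges per distribution"), but not how they are tested.

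**The concern.** Stratified blocks force the arms to be nearly balanced on urgency, so urgency contributes almost nothing to the sampling error of the treatment difference. A t-test that ignores the stratum still counts the elective–emergency difference as noise. Its standard error is therefore too large whenever urgency is prognostic.

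That urgency matters here is plausible from the article itself. The Discussion concedes that mixing elective and emergency cases brings clinical heterogeneity, and urgency was chosen as the sole stratification factor. The article gives no size for the effect.

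At stake is the chance of showing a real shortening of stay or a real fall in potassium need. Holm's first step in a family of three is 0.05/3 = 0.0167, so absolute power is already lower than at 0.05.

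**Working it through.** **The plan's own figures.** The article states no SD, skewness, urgency effect or power for any Family B outcome, so there is no figure of that kind to reproduce. The primary-endpoint calculation does reproduce and is not in dispute:
- n per arm = 2 × (1.960 + 0.842)² × 400² / 250² = 40.2, so 41.
- With 15% dropout, 41 / 0.85 = 48.2, so 49.
- Power at 50 per arm: 250 / (400 × √(2/50)) = 3.125, and Φ(3.125 − 1.960) = 87.8%, against 87.5% stated.

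**Assumed inputs, none of them in the article.** Stay is lognormal with log-SD (sigma) 0.5 or 0.6. The elective median is 6 days and the emergency median 9 or 12. The emergency share is 40% and the true effect is a 25% shorter stay. There are 42 evaluable per arm (50 × 0.85 = 42.5). Tests are two-sided at 0.05. The only stay figure in the article is in Table 2, for the standard arm, 5–10 days being typical.

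**Why the t-test is conservative.** Write W for the within-stratum variance, B for the between-stratum variance and N for the total number of patients.
- With arms balanced within strata, the true variance of the difference in means is (4/N) × W.
- The unstratified t-test estimates it as (4/N) × (W + B).
- The standard error is therefore too large by √(1 + B/W), and the approximate type I error is 2 × [1 − Φ(1.96 × √(1 + B/W))].

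For a lognormal, mean = median × exp(sigma²/2) and variance = mean² × (exp(sigma²) − 1). For sigma 0.5 and 6 v 9 days:
- Means are 6.80 and 10.20.
- W = 0.6 × 13.13 + 0.4 × 29.54 = 19.69.
- B = 0.6 × 0.4 × (10.20 − 6.80)² = 2.77.
- B/W = 0.141, so the standard error is 1.068 times too large and type I error is about 3.6%.

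The four cases by the same formula:

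| Median stay | Sigma | W | B | SE too large by | Approx. type I error |
|---|---|---|---|---|---|
| 6 v 9 | 0.5 | 19.69 | 2.77 | 7% | 3.6% |
| 6 v 9 | 0.6 | 33.54 | 3.10 | 5% | 4.1% |
| 6 v 12 | 0.5 | 28.88 | 11.09 | 18% | 2.1% |
| 6 v 12 | 0.6 | 49.19 | 12.38 | 12% | 2.8% |

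Simulation agrees: about 3.7% at 6 v 9 and about 2–2.6% at 6 v 12.

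**Power from the stratum term alone (simulated, mean-difference scale kept).**

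| Median stay | Sigma | t-test | Linear model with stratum | Gain (points) |
|---|---|---|---|---|
| 6 v 9 | 0.5 | 62% | 67% | 5 |
| 6 v 9 | 0.6 | 47% | 51% | 4 |
| 6 v 12 | 0.5 | 50% | 65% | 15 |
| 6 v 12 | 0.6 | 38% | 48% | 10 |

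**Wider range.** A separate simulation used log-SD 0.4–0.8, an emergency/elective ratio of 1.5–2.0 and 30–50% emergency. The stratum term gained about 1–18 points. With a ratio of 1.0 the two analyses had the same power (for example 52.9% each at log-SD 0.6), so nothing is lost. The stratum-adjusted analyses held type I error at about 4–6%.

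**Potassium.** The assumptions were 30–50% zeros in controls, 15 points more zeros in the intensified arm, lognormal amounts otherwise with a treatment ratio of 0.75, and an emergency/elective ratio of 1.5–2.0. The t-test had 31–39% power and the stratum term added only 0–3 points.

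**The case against.** **The larger gains belong to the scale, not the stratum.** A reader might set the raw t-test against a log-scale model with stratum and put the whole difference down to ignoring the randomisation. At 6 v 9 days and sigma 0.5 that comparison is 62% v 75%, but the stratum accounts for only about 5 of the 13 points. The rest comes from moving to the log scale, which tests a ratio of geometric means. A van Elteren test likewise tests ordering. Mean days and mean potassium are defensible targets for resource outcomes, so the choice of scale is a trade-off and not an error. This objection stands, and the point is confined to the stratum term.

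**The inputs are assumed.** The article does not say how skewed these outcomes are or how strongly urgency predicts them. A 25% shorter stay is also generous when both arms receive omeprazole. This stands: the direction follows from the design once urgency is prognostic, but the size does not come from the article.

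**Low stakes.** The trial is not powered on secondary outcomes, and the Discussion calls a list of them exploratory. This stands in part. The Endpoints paragraph counts length of stay among the key secondary endpoints, and Family B has formal multiplicity control.

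**Condensed article.** Handling of strata could sit in an analysis plan that is not shown. That weakens the point but does not remove it, because the article itself names the test.

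**Conclusion.** The concern holds as a modest loss of efficiency. The article fixes unstratified t-tests for all of Family B after stratifying randomisation by urgency. If urgency is prognostic, intervals are too wide and the tests are conservative. For stay, under the stated assumptions, the stratum term is worth about 4–5 points of power for a 6 v 9 day contrast and 10–15 points for 6 v 12. It is worth nothing if urgency does not matter. For potassium it is worth about 0–3 points.

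Two stronger readings are not supported. One is that the t-tests risk false-positive claims: the error runs the other way, and with roughly 42–50 per arm the simulations show no inflation despite the skew. The other is that urgency is known to be a strong driver of stay and potassium need: the article acknowledges heterogeneity without measuring it. Nor is urgency overlooked altogether, since exploratory analyses by urgency are planned, although they do not replace an adjusted comparison.

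**What to change.** Replace each of the three t-tests by a linear model with arm and admission type as randomised. Report the adjusted mean difference with a 95% confidence interval, using robust or stratified-bootstrap standard errors because of the likely skew. Feed the resulting p-values into the Holm procedure for Family B. The estimand stays a difference in means.

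Optionally, add a log-scale model with stratum for stay, and a van Elteren test stratified by admission type for potassium, where zeros rule out a plain log. Label both as sensitivity analyses, because they test a different quantity.

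The cost is wording. Admission type is already recorded for randomisation, and no patients, visits or measurements are added. Recruitment is expected to run to July 2027, so the change can be documented before the final comparison by arm is seen.

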## 4. Discussion

High-output stoma remains a frequent and clinically important complication after the creation of an ileostomy, causing fluid and electrolyte losses, secondary hyperaldosteronism, hypokalemia, hyponatremia and AKI, which in turn precipitate unplanned care and readmissions [7,32]. A recent review characterizes HOS as a “secretory” complication and reports incidences in the range of ~14–24% when defined by outputs between 1.0 and 2.0 L/day over several days, underscoring both the burden and variability introduced by non-uniform thresholds. Post-ileostomy readmission for dehydration or renal failure is common [33]; in historical series, ~17% of patients were readmitted within 30 days specifically for these indications, and AKI has been recognized as a frequent readmission diagnosis in contemporary datasets [7,8,33,34]. Major society guidance and practice updates emphasize structured fluids and electrolyte management, oral rehydration solutions with adequate sodium concentration, and early use of antimotility and antisecretory agents as core elements of care, reflecting convergence of expert practice even as high-grade trial evidence remains limited [10,21,35].

The physiologic rationale supports the use of proton pump inhibitors to mitigate effluent in settings of net intestinal secretion. In patients with extensive small-bowel resection, a population similar to early high-output ileostomies, intravenous omeprazole increased net water and sodium absorption versus no therapy or ranitidine in a randomized crossover experiment, with the greatest effect in those with high outputs (“net secretors”) [16]. Narrative and practice-oriented reviews for HOS management list PPIs alongside loperamide and codeine in stepped algorithms, aiming to reduce gastric and small-bowel secretions and thereby decrease effluent volume [10,35]. However, to our knowledge, no randomized trial has tested intensified PPI dosing in the immediate postoperative ileostomy population to prevent or attenuate HOS; therefore, high-quality interventional data specific to this question are lacking. STOP-HOS-1 is designed to address this gap.

The trial focuses on a clinically early postoperative window when output is most unstable and fluid or electrolyte disturbances carry the greatest clinical consequences. It compares an intensified intravenous omeprazole regimen with standard dosing in a pragmatic, multicenter, randomized, open-label design. The quantitative primary endpoint (mean 24 h output across POD 1–3, with a prespecified clinically meaningful difference of ≥250 mL/day) was selected because it reflects a physiological parameter directly informing bedside decisions, including oral fluid restriction, intravenous supplementation, and timing or escalation of antimotility therapy.

The targeted effect size, therefore, represents a pragmatically defined and clinically actionable reduction aligned with thresholds commonly guiding supportive management in routine practice.

Allocation concealment, standardized perioperative care pathways (including electrolyte monitoring, oral rehydration solutions, and stepwise antimotility therapy), a unified eCRF, and dedicated data collectors were implemented to reduce bias and improve measurement reliability, addressing methodological limitations frequently encountered in observational studies of ileostomy output. Nevertheless, the pragmatic perioperative setting requires individualized supportive care. Although fluid therapy, dietary adjustments, and antimotility escalation are prospectively recorded within a structured monitoring framework, variability in post-randomization clinical management cannot be entirely eliminated and should be considered when interpreting treatment effects. While the open-label design may introduce performance effects, the primary endpoint is objective and supported by prespecified intention-to-treat and per-protocol analyses with sensitivity assessments. At the same time, ileostomy output—measured through routine bedside assessment—may be subject to non-differential inter-observer variability, potentially attenuating detectable between-group differences. Moreover, the primary endpoint represents a physiological surrogate rather than a direct patient-centered outcome, and follow-up is limited to early postoperative recovery; longer-term quality of life and morbidity therefore remain beyond the scope of the present study. Inclusion of both elective and emergency procedures enhances external validity but introduces clinical heterogeneity reflecting real-world surgical populations. Because the study is not powered for definitive subgroup comparisons, any apparent variation in treatment effect across surgical contexts should be interpreted cautiously as exploratory. Similarly, incomplete POD 1–3 measurements related to early discharge, clinical deterioration, or perioperative mortality may occur despite prospective monitoring. Multiple imputation and prespecified sensitivity analyses were incorporated to mitigate bias related to missing data, although imputed values inherently introduce additional uncertainty, particularly when treatment effects are modest. The modified intention-to-treat framework further reflects pragmatic feasibility while requiring transparent interpretation with respect to potential attrition-related bias.

The study is adequately powered for a physiological endpoint, whereas secondary outcomes—including HOS incidence, dehydration-related complications, and 30-day readmissions—are analysed exploratorily; observed associations should therefore be considered hypothesis-generating pending confirmation in adequately powered trials. Conduct within two academic centers may also influence generalizability where postoperative pathways differ, despite standardized guideline-based management.

Given that both groups receive perioperative PPI prophylaxis as part of standard care and short-term intensified dosing has not been associated with a materially increased risk of serious adverse events, safety monitoring in STOP-HOS-1 prioritizes the detection of unexpected or imbalanced adverse events rather than predefined numerical stopping thresholds for rare complications [26].

Positive findings would be readily implementable and could strengthen the evidentiary basis for HOS management algorithms that currently rely largely on physiologic reasoning and lower-grade evidence. Conversely, neutral results would be equally informative, prompting the reconsideration of routine PPI escalation in early postoperative ileostomy care and redirecting attention toward alternative or combined strategies, including optimized oral rehydration, structured antimotility pathways, or phenotype-targeted treatment approaches such as biologically defined “net secretor” populations. In sum, STOP-HOS-1 directly tests an intuitive, low-cost, and scalable intervention embedded in routine postoperative care. By anchoring decision-making to quantitative effluent outcomes and clinically relevant complications, the trial aims to generate evidence capable of either reinforcing current practice where justified or recalibrating it where benefit is not supported by high-quality data.

Trial Status: The first version of the protocol was registered at ClinicalTrials.gov (NCT06917963) on 5 April 2025. Recruitment started on 10 April 2025 and is expected to conclude by July 2027.

